## 1. Summary

Folate intake may be marginal in subgroups of the western population, and a noninvasive method for the screening of folate status would allow for easier and less cumbersome assessment, than the identification via the established markers serum or red blood cell folate concentration. Such a method could be applied in epidemiological studies and in large clinical trials including children.

Markers, which seem suitable for this purpose are urinary excretion of formiminoglutamate (FIGLU) and para-aminobenzoylglutamate (p-ABG), which are an intermediate of folate dependent conversion of histidine to glutamate or a catabolite of folate, respectively. In case of folate deficiency urinary excretion of FIGLU is increased after a histidine load and clinical trials have shown increased total p-ABG excretion after increased folic acid intake. Thus we plan to test the suitability of these markers by analyzing red blood cell and serum folate concentration as well as 24-h urinary excretion of FIGLU and p-ABG in 50 healthy, adult men. The participants will deliver a spot urine sample and a blood sample at their first study visit, while at the second visit (21 days later) they will provide the collected urine of the last 24 hours, a further spot urine sample and a second blood sample. This enables testing of short time variation of circulating markers. Furthermore, this enables a comparison of the results obtained by direct measurement of 24-h urinary excretion with estimation of 24-h excretion from a single sample with adjustment via urinary creatinine concentration. These measurements are used to evaluate the applicability of urinary FIGLU and p-ABG as indicators of folate status for screening purposes.

In the supplementation part of the study from those participants in the lowest quartile of RBC folate level and from those in the highest quartile of RBC folate 10 subjects will be selected each, for participation in a folic acid supplementation trial. These subjects will consume daily a 400 µg folate supplement for 12 weeks. Their urinary and blood folate markers will be analysed after 6 weeks and 12 weeks to evaluate the suitability of FIGLU and p-ABG excretion as indicators of folate level in supplementation studies. The relationship between circulating and urinary markers will be statistically evaluated by analysis of correlation and by receiver operator characteristics analysis.

If suitability of these new markers could be demonstrated, this would provide an additional tool for folate screening and for use in clinical trials.

.

## 3. Introduction

The importance of folate mediated one-carbon metabolism in metabolic and cellular processes has long been recognized and epidemiological, genetic and biochemical studies have revealed that folate status is related to the incidence of certain cancers, birth defects and cardiovascular disease (Stover, 2004). Folate occurs in the cells as several structurally related derivatives comprised of 2-amino-4-hydroxypteridine linked to p-aminobenzoylglutamate. Reduced tetrahydrofolates serve as cofactors that deliver one-carbon units at different oxidation levels. Reduced tetrahydrofolate may have a one-carbon substituent, such as a methyl-, formyl- or formimino- group at N5 or a methylene or methenyl bridge between N5 and N10. These substituents form a pool of activated one carbon units. They are transferred to other molecules in a variety of biochemical reactions. While in serum folate has a monoglutamyl residue, intracellularly folate usually occurs with 5–8  $\gamma$ -linked glutamyl residues. The polyglutamate moiety seems important for proper function of the coenzyme. Most of the intracellular folate by far is protein bound (Matherly et al, 1990). In rats it has been demonstrated that tight folate binding proteins are highly or exclusively expressed in the liver, thus liver may contain up to one half of total body folate (Gregory, III et al, 1998). As non protein bound intracellular folate is negligible, this also indicates that intracellular folate is limited by folate-binding capacity and independent of excessive exogenous folate supply (Suh et al, 2001).

Folate is important for the transfer of one-carbon units, as required for the de novo synthesis of purines and thymidine and for the remethylation of homocysteine to yield methionine. Further biochemical reactions, which require folate as a cofactor are conversion of serine to glycine and histidine breakdown, yielding as an intermediate  $\gamma$ -

formiminoglutamic acid (FIGLU), which needs folic acid as a formyl acceptor for conversion to glutamic acid.

As mammals can not synthesize folate *de novo*, a dietary supply is required. Naturally occurring folate has a reduced pteridine ring and a polyglutamate residue, which has to be hydrolysed intestinally to monoglutamate before absorption, while synthetic folate is provided with a fully oxidised pteridine ring and only one glutamate residue. After reduction to tetrahydrofolate it is equivalent in its biological function to natural folate.

Folate deficiency disrupts folate requiring pathways, such as homocysteine remethylation and thymidylate synthesis, and leads to identifiable pathologies. Thus, plasma homocysteine level is a sensitive biomarker for folate status, if availability of vitamins B2 (riboflavin), B6 (pyridoxine) and B12 (cobalamin) is adequate (Brosnan, 2004). Impaired conversion of homocysteine to methionine leads to accumulation of S-adenosylhomocysteine, which inhibits S-adenosylmethionine dependant reactions, including DNA methylation. The relationship between folate status and neural tube defects is well established, with folic acid supplementation decreasing the incidence significantly (Tamura et al, 2006).

Direct biochemical indicators of folate status are serum and red blood cell (RBC) folate levels. Serum folate represents circulating folate, which can change quickly and is directly influenced by diet, whereas RBC folate level is assumed to represent folate stores (Hoey et al, 2007). RBC folate is a good indicator of long term status, because cellular folate stores accumulated during erythropoiesis are retained throughout the lifespan of the erythrocyte. It has been demonstrated in rats that RBC and hepatocyte folate levels strongly correlate (Picciano et al, 1995). In humans a clear relationship between RBC folate and the incidence of neural tube defects could be shown (Daly et al, 1995).

Beyond these established markers, it would be desirable to obtain a reliable estimate of the folate status via non invasive markers, which can easily be collected and applied in a large number of subjects including children. Folate intake may be marginal in subgroups of the western population, and a noninvasive method for the screening of folate status would allow for easier and less cumbersome assessment. Furthermore, such a screening tool would allow to assess, if people are exposed to high doses of folic acid, which has been raised as a concern in elderly, in countries with folic acid fortification. Buccal cell folate has been considered suitable, but correlation with RBC folate has been found to be poor and buccal mucosa folate did not show any effect of 12 weeks of supplementation with 1.2 mg folic acid per day (Basten et al, 2004). As an alternative, urine can be sampled noninvasively and concentrations of folate and homocysteine can be determined. Urinary homocysteine concentrations seem not to be related to plasma total homocysteine concentrations (personal communication, [name], Paediatrics and Nutritional

Sciences, University of Toronto, Canada; and [name], Department of Pharmacology, University of Bergen, Norway). 24-h urinary excretion of folate was reported to decline significantly in Mexican American men within 6 weeks after onset of a controlled diet, which provided 418 µg/d of dietary folate equivalents (Solis et al, 2008). At the same time significant decreases of serum and RBC folate were observed. Although this suggests applicability of urinary folate excretion as an indicator of folate status, there is large interpersonal variation in the amount excreted and excretion might depend on methyltetrahydrofolate reductase genotype (Yang et al, 2005; Guinotte et al, 2003). This seems to limit the predictive value of folate excretion for folate status. Urinary excretion of FIGLU is known to be elevated after a histidine load, in case of folate deficiency (Cooperman et al, 2002). Although in a previous study no significant correlation of FIGLU excretion, with other markers of folate status could be demonstrated (Pietrzik et al, 1980), improved analytical techniques (LC-MS/MS) warrant a reconsideration. However, the most promising biomarker of folate status in urine might be folate catabolites (Bailey et al, 1999). Although not polyglutamated folate can efflux from the cell either directly after entering the cell or after hydrolysis by γ-glutamylhydrolase, non reversible folate catabolism proceeds via non enzymatic or potentially enzyme catalysed cleavage of the C9-N10 bond of dihydrofolate, yielding a pterin aldehyde and p-aminobenzoylglutamate (Suh et al, 2001). While the pterin residue is retained in the liver and only slowly released, the export of p-aminobenzoylglutamate (p-ABG) out of the cells is facilitated by removal of the polyglutamate and the majority of p-ABG is acetylated at the amino group catalysed by arylamine N-acetyltransferase. Acetylated p-ABG (Ap-ABG) does not accumulate in cells and is rapidly excreted in urine (Murphy et al, 1976). In rats Ap-ABG concentration in urine is considered a reliable marker of folate status and turnover (Wang et al, 1994). Results in humans are not fully supporting the hypothesis that urinary total p-ABG is a good indicator of folate status and/or intake, because catabolite excretion might reflect changed intake only after some delay as total p-ABG (Ap-ABG and p-ABG) originates from slow turnover pools (Gregory, III et al, 2000). Thus, effects of short term interventions might not be detected by the analysis of urinary p-ABG, but a correlation with a long term marker such as RBC folate, can be assumed. Furthermore, tracer experiments with deuterated folic acid demonstrated that turnover of folate pools in humans increases with increasing intake, thus an increased catabolite excretion can be expected (Gregory, III et al, 1998). In a study in postmenopausal women, involving 7 week periods of folate depletion (intake 120 µg/d) and repletion (intake 200 µg/d or 400 µg/d) significant correlations between serum folate, RBC folate and urinary excretion of catabolites were observed (Wolfe et al, 2003). These findings were obtained with 24h urine collections, thus it will be tested whether FIGLU or total p-ABG concentrations in spot urine samples can be extrapolated to 24 h excretion via urinary creatinine concentration (Bingham et al, 1988). This is of

importance as in large clinical trials or in population screening only collection of spot samples is feasible.

So far wider application of FIGLU and p-ABG as markers in clinical studies was limited by demanding analytical procedure (McPartlin et al, 1992), but with the availability of a LC-MS/MS based methods (Sokoro et al, 2006; Bishop et al, 2007; Hannisdal et al, 2008), which enable high sample throughput, application of urinary FIGLU and p-ABG as a non-invasive markers of folate status has become possible and corresponding validation studies are warranted.

#### **4. Objectives**

The major objective of the proposed study is to demonstrate the suitability of new markers for folate status in humans, which avoid blood sampling, as required for the established marker RBC folate concentration, but can be obtained from spot urine samples.

Specific hypotheses to be tested:

Correlation study:

- a) The 24 h urinary excretion of total p-ABG, as extrapolated via urinary creatinine concentration from the total p-ABG concentration in a spot sample is significantly correlated to RBC and plasma folate levels in the studied subjects
- b) The 24 h urinary excretion of FIGLU, as extrapolated via urinary creatinine concentration from the FIGLU concentration in a spot sample is significantly correlated to RBC and plasma folate levels in the studied subjects

Intervention study:

- a) changes in folate status (RBC folate) after supplementary intake of folate result in increased urinary excretion of total p-ABG and FIGLU in subjects identified with a low folate status and in subjects identified with a high folate status among the study participants of the correlation study

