The obtained coefficients are the primary criterion for the applicability of the latter parameters as indicators of the subjects folate status. For a more detailed analysis of the data multiple regression analysis with RBC folate as the independent parameter and urinary excretion of total p-ABG or FIGLU as dependent variable including correction for other potentially confounding factors (e.g. vitamin B12, vitamin B6, age) will be performed. For these detailed analyses the support of an experienced biostatistician will be sought.

For evaluation of the time course of blood and urine markers of folate status repeated measures analysis of variance will be performed, with group allocation (high or low folate status according to RBC folate) as an independent factor. Furthermore, correlation analysis as described for the basal values will be performed, to investigate the suitability of urinary folate markers under conditions of a defined recent change of folate intake.

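### The intervention hypothesis predicts that folic acid raises urinary FIGLU, while the protocol's own rationale makes FIGLU fall as folate status improves

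*Protocol*

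**What the plan says.** Section 4 of the Protocol (Objectives) lists the specific hypotheses. The intervention part has one: changes in RBC folate after extra folate intake will "result in increased urinary excretion of total p-ABG and FIGLU in subjects identified with a low folate status", and the same is said of subjects identified with a high status. The one word for the direction covers both markers and both groups.

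The rationale treats the two markers differently.

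- FIGLU, section 1: "In case of folate deficiency urinary excretion of FIGLU is increased after a histidine load".
- FIGLU, section 3: "Urinary excretion of FIGLU is known to be elevated after a histidine load, in case of folate deficiency". The same section describes it as "formiminoglutamic acid (FIGLU), which needs folic acid as a formyl acceptor for conversion to glutamic acid".
- p-ABG, section 3: "turnover of folate pools in humans increases with increasing intake, thus an increased catabolite excretion can be expected".

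The correlation hypothesis for FIGLU gives no sign. It says only that the extrapolated 24 h excretion "from the FIGLU concentration in a spot sample is significantly correlated to RBC and plasma folate levels in the studied subjects". The intervention analysis in section 9 gives none either: "For evaluation of the time course of blood and urine markers of folate status repeated measures analysis of variance will be performed", with folate-status group as a factor, followed by correlations as at baseline.

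**The concern.** If folate is needed to convert FIGLU, and FIGLU excretion is high when folate is short, then better folate status should lower FIGLU or, in people who already have enough, leave it where it is. The hypothesis says it will rise.

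What is at stake is the reading of the result. Section 6.2 sets up the intervention part to find out whether both markers can show changes in folate status, and section 10 presents the supplementation follow-up as a possible external validation. Held against the hypothesis as written, FIGLU data that fit the stated mechanism refute it, and data that contradict the mechanism confirm it. If the direction is corrected only after the results are known, the correction is open to challenge as post hoc.

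**Working it through.** The point is about direction, so the main check is to set the statements side by side.

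| Marker | Rationale (sections 1 and 3) | Implied response to more folate | Hypothesis (section 4) |
|---|---|---|---|
| Total p-ABG | Excretion rises with intake and turnover | Increase | Increase |
| FIGLU | Raised in deficiency after a histidine load; needs folate for conversion | Decrease, or no change if replete | Increase |

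The p-ABG row agrees and the FIGLU row does not. No statement elsewhere in the protocol predicts more FIGLU with more folate. The nearest neutral remark, in section 3, is that a previous study found no significant correlation between FIGLU and other folate markers. That speaks for a weak relationship, not for a positive one.

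**Does any stated figure depend on this hypothesis?** Section 5.1 gives the only sample size: r = 0.35, power 80%, α = 0.05, n = 49, and it is based on the correlation study. With the Fisher z formula n = ((z_α + z_power) / atanh(r))² + 3 and atanh(0.35) = 0.3654:

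- one-sided: ((1.645 + 0.842) / 0.3654)² + 3 = 49.3
- two-sided: ((1.960 + 0.842) / 0.3654)² + 3 = 61.8

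The stated 49 is therefore close to the one-sided result. It belongs to another part of the study, and no power statement is made for the intervention.

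**Can the planned analysis see a fall?** The protocol gives no expected FIGLU change, so I assume a true fall of 0.5 to 1.0 SD of the within-subject change. As a simple stand-in for the time effect in the repeated measures analysis I use a two-sided paired t-test at 5%. Section 6.2 gives 10 subjects per group and 20 in all.

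| Assumed fall (SD) | Power, n = 10 | Power, n = 20 |
|---|---|---|
| 0.5 | 29% | 56% |
| 0.8 | 62% | 92% |
| 1.0 | 80% | 99% |

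So a non-directional test can detect a fall, subject to the usual limits of small groups. By contrast, a one-sided 5% test for an increase would succeed with probability below 0.1% for every fall in this range, at either sample size. The protocol does not plan such a test.

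**The case against.** The strongest defence is that the sentence is loosely worded and changes nothing that will be done. No visit, sample, test or sample size rests on it. Section 6.2 states the aim without a direction, and section 9 takes the coefficients from the correlation and ROC work as the primary criterion of applicability. On those passages a fall in FIGLU alongside rising RBC folate would read as support. This stands as a limit on the consequences. It does not remove the contradiction, because the sentence is the only hypothesis stated for the intervention part.

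A second objection is that the inverse relationship is documented only after a histidine load, and no load is planned. The participants are healthy men, and one group is drawn from the highest RBC folate quartile. A fall is therefore not established, least of all in that group. This also stands, and it shapes the fix, but it gives no support for an increase.

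A reader might infer two stronger points that the document does not support.

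- *A true fall in FIGLU cannot be detected, because testing is one-sided.* The argument would rest on n = 49 fitting only the one-sided formula. Section 5.1 does not state sidedness and concerns the correlation study; section 9 states no direction for the intervention analysis. The tiny success probability of a one-sided test for an increase describes a test that nobody has planned.
- *The FIGLU correlation hypothesis and the ROC analysis carry the same sign error.* The correlation hypothesis is compatible with a negative coefficient. Section 9 names the lowest RBC folate quartile as the reference classification and gives no wrong test-positive side. Fixing that orientation can be left to a statistical analysis plan.

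**Conclusion.** The contradiction is real and stands in the current text: the predicted direction for FIGLU in the intervention hypothesis is opposite to the one that the protocol's rationale implies, and nothing in the document supports the stated direction. The effect is confined to how the FIGLU result is scored against the hypothesis. Detection of a fall is not affected, and no stated sample size, power or error rate changes. The conclusion rests on the ordinary reading that the predicted increase applies to both markers, and on the protocol's own account of FIGLU. It does not require that FIGLU will in fact fall without a histidine load.

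**What to change.** Reword intervention hypothesis a) in section 4 before any data are seen, with a direction for each marker:

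- total p-ABG excretion: increase, as now;
- FIGLU excretion, low-status group: decrease;
- FIGLU excretion, high-status group: change tested two-sided, with no direction predicted, since no histidine load is planned and absence of change is plausible in replete subjects.

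As an optional edit for consistency, the FIGLU correlation hypothesis could name the expected negative sign, and the ROC description could say that high FIGLU and low p-ABG are the test-positive side. Neither corrects an error.

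The cost is one reworded hypothesis. Visits, samples, subject numbers and the planned analysis of variance stay as they are.

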#### **5. Participating subjects**

##### **5.1. Subject number**

The sample size estimation is based the correlation study. It is assumed that a correlation of at least 0.35 would be sufficient to use urinary total p-ABG or FIGLU as markers for

folate status. To detect such a correlation as statistically significant with a power 80% and  $\alpha$  of 0.05 samples from 49 subjects have to be analyzed (Uitenbroek, Daan G, Binomial. SISA. 1997. <http://www.quantitativeskills.com/sisa/distributions/binomial.htm>. (1 Jan. 2004). Thus, 50 subjects will be enrolled into the correlation study and from these participants for the intervention study will be selected.

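### The correlation of 0.35 that section 5.1 calls sufficient for using the urine markers shows association with RBC folate, but does not support suitability for screening individuals

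*Protocol*

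**What the plan says.** The main objective, in section 4, is about suitability: "The major objective of the proposed study is to demonstrate the suitability of new markers for folate status in humans". Under it, the two correlation-study hypotheses are that the spot-estimated 24-h excretion of each urine marker "is significantly correlated to RBC and plasma folate levels in the studied subjects". They name no minimum size.

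Section 5.1 supplies the only number: "It is assumed that a correlation of at least 0.35 would be sufficient to use urinary total p-ABG or FIGLU as markers for" folate status. The sample size follows from it: "To detect such a correlation as statistically significant with a power 80% and" alpha "of 0.05 samples from 49 subjects have to be analyzed". "Thus, 50 subjects will be enrolled into the correlation study".

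Section 9 calls correlation and ROC analysis together the major focus of the evaluation. It takes the lowest RBC-folate quartile as gold standard, lists sensitivity, specificity and both predictive values, and compares parameters by AUC. The next sentence reads: "The obtained coefficients are the primary criterion for the applicability of the latter parameters as indicators of the subjects folate status". No minimum is given for the AUC or any accuracy measure.

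The summary (section 1) and section 10 name screening as an intended use, alongside clinical trials and epidemiological studies.

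**The concern.** Screening for low folate status classifies individuals. A correlation coefficient describes how two markers move together across a group, and a modest one can go with poor classification. Section 5.1 nevertheless ties 0.35 to use of the marker, not merely to what the study can detect, and section 9 puts the coefficients first when applicability is judged.

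If the study observes a correlation of 0.35 or a little more, the text as written allows the conclusion that the marker is suitable, with screening as one of the stated uses. The question is how well a marker at that value would find men in the lowest RBC-folate quartile.

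**Working it through.** **Inputs from the protocol.** Correlation 0.35, power 80%, alpha 0.05, 49 subjects needed and 50 enrolled (section 5.1). Condition to be detected: lowest quartile of RBC folate, so prevalence is 25% by definition (section 9).

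**Assumptions not in the protocol.** RBC folate and the urine marker are bivariate normal after the transformation that section 9 allows. A urine test is positive at the end of the scale that points to deficiency, so for FIGLU, expected to rise in deficiency, r is read as an absolute value. The protocol fixes no urine cut-off, so three are shown.

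**The plan's own figure.** Fisher's z gives n = ((z_alpha + z_power)/atanh(r))² + 3, with atanh(0.35) = 0.3654.
- One-sided 0.05: ((1.645 + 0.842)/0.3654)² + 3 = 49.3, which matches the stated 49.
- Two-sided 0.05: ((1.960 + 0.842)/0.3654)² + 3 = 61.8, that is 62.

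The 49 therefore reproduces as a one-sided calculation with 0.35 as the effect size. Sidedness is not stated, and the present point does not depend on it.

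**Shared variance.** r² = 0.35² = 0.1225, or 12%.

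**Accuracy at r = 0.35.** Let J(f) = Φ₂(z₀.₂₅, z_f; r) be the probability that a man is in the lowest RBC-folate quartile and also among the fraction f flagged by the urine test. Then sensitivity = J/0.25 and specificity = 1 − (f − J)/0.75.

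| Urine cut-off | Sensitivity | Specificity |
|---|---|---|
| Flags 25% of men (J = 0.1011) | 0.1011/0.25 = 40.4% | 1 − (0.25 − 0.1011)/0.75 = 80.1% |
| Youden-optimal (flags about 45%) | 63.2% | 60.9% |
| Sensitivity held at 80% (flags about 64%) | 80% | 41.4% |

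A test that flags 25% of men at random would have 25% sensitivity. Integrating over all cut-offs gives AUC = 0.668. For comparison, r = 0.80 gives AUC 0.89 and specificity 81% at 80% sensitivity.

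**Precision of an observed r = 0.35 at n = 50.** tanh(0.3654 ± 1.96/√47) gives a 95% interval of 0.08 to 0.57.

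**Precision of the AUC.** A quarter of 50 is 12.5, so 12 or 13 men are in the lowest quartile. By Hanley–McNeil, Var = [A(1 − A) + (n₁ − 1)(Q₁ − A²) + (n₂ − 1)(Q₂ − A²)]/(n₁n₂), with A = 0.668, Q₁ = A/(2 − A) = 0.5015 and Q₂ = 2A²/(1 + A) = 0.5350. With n₁ = 13 and n₂ = 37 the standard error is 0.092, and the 95% interval is 0.668 ± 1.96 × 0.092, about 0.49 to 0.85. With 12 and 38 it is about 0.48 to 0.85.

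**The case against.** The strongest reply is that the protocol does not rest on correlation alone. Section 9 gives ROC analysis equal place with correlation, and section 10 says that cut-off values must also be established before the marker is used as a screening tool. The 0.35 is introduced as an assumption under the sample-size heading, and section 9 never repeats it. The sentence on coefficients directly follows the ROC sentences and does not say which coefficients it means. Much of this stands: poor accuracy would be visible in the report. It does not remove the wording of section 5.1, which speaks of use and not of detection, nor does it give the ROC results a clear place in the criterion.

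Group-level use is also fairly raised. Epidemiological studies and trials are named too, and individual misclassification is not the deciding measure there. The point is therefore confined to screening individuals.

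Three stronger readings are tempting and are not supported:

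- A reader might infer that any significant correlation would count as sufficient. With 50 men the two-sided limit is r = 0.28 (2.011/√(48 + 2.011²)). Such a value would satisfy a section 4 hypothesis but fall short of 0.35, the only sufficiency value stated.
- A reader might conclude that the marker simply misses 60% of low-folate men. That holds only for a cut-off flagging 25% of men, under the normal model; at the Youden cut-off about 37% are missed, with about 39% of the other men flagged falsely.
- A reader might see a contradiction with the introduction: "Buccal cell folate has been considered suitable, but correlation with RBC folate has been found to be poor". No coefficient is given there, and a second reason, lack of response to supplementation, is added. The comparison settles nothing.

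**Conclusion.** The point holds for screening individuals. At r = 0.35 the implied AUC is about 0.67, and none of the three cut-offs examined combines good sensitivity with good specificity: about 40% and 80%, 63% and 61%, or 80% and 41%. The threshold in section 5.1 therefore supports a statement of association with RBC folate and not one of suitability for screening.

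The figures rest on bivariate normality after transformation and on the protocol's own gold standard. The reading of section 9 rests on taking its coefficients to be correlation coefficients, which is natural but not explicit. If ROC measures are meant as well, there is still no stated pass mark, and 0.35 remains the only number attached to sufficiency.

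It would go too far to say that the plan is bound to declare an unusable test suitable. The ROC results will be reported, section 10 asks for cut-off values first, and what counts as unusable is a judgement. Data collection is not affected; the defect lies in the stated threshold and criterion.

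**What to change.** - **Section 5.1:** describe 0.35 as the smallest correlation of interest for the sample size, and say that reaching it shows association, not suitability for screening.
- **Section 9:** say which coefficients are meant. State that applicability for screening is judged on the planned ROC results (AUC, and sensitivity at a fixed specificity) for spot-estimated excretion against the lowest RBC-folate quartile. Set a minimum point estimate before analysis, and report confidence intervals.
- **Conclusions:** from correlation alone, claim only that the marker is associated with RBC folate.

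Do not adopt a rule that the confidence interval need only be compatible with the minimum. With 12 to 13 men in the lowest quartile, an AUC of 0.67 has an interval of about 0.49 to 0.85, so a minimum of, for example, 0.80 would lie inside it and the marker would pass. For the same reason, describe a positive ROC result as preliminary.

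The cost is wording only, with no extra subjects or samples. The downside is that a claim of suitability becomes harder to reach.
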